## Abstract

**Background:**

Protein is an essential macronutrient with an important role during complementary feeding. Low protein intake contributes to undernutrition while high intake, especially from animal sources, may increase obesity risk. However, the influences of different protein sources (dairy, meat, and plants) on growth, and underlying mechanisms for these effects, are poorly understood. Animal-sourced foods provide both high-quality protein and iron and are recommended to improve iron status. However, it is unclear whether current dietary recommendations are adequate to support healthy growth and optimize iron status. These issues are of particular concern in countries facing the double burden of malnutrition, the coexistence of all forms of malnutrition. More evidence is needed to develop appropriate recommendations for these countries.

**Objective:**

This study will investigate associations between protein intake during complementary feeding and growth, body composition, and iron status of infants in Thailand, a country facing the double burden of malnutrition. The study will also explore how different protein sources influence growth via the growth hormone—insulin-like growth factor I (IGF-1) axis and plasma amino acids.

**Methods:**

A multicenter cohort study will be conducted in Chiang Mai, Thailand, in 150 healthy term infants aged 4-6 months with birth weight ≥2500 g. Demographic data, dietary intake, and anthropometry will be collected at 6, 9, and 12 months. Dietary intake will be assessed using 24-hour dietary recalls, 3-day food records, and food frequency questionnaires. Blood samples for iron status, growth hormone, IGF-1, insulin-like growth factor-binding protein III (IGFBP-3), and plasma amino acids and urine samples for body composition analysis using stable isotope dilution will be obtained at 12 months.

**Results:**

The recruitment of study participants and data collection was undertaken from June 2018 to May 2019. Data and laboratory analyses are ongoing and are expected to be completed by December 2020. A total of 150 participants were enrolled, and 146 completed the study. We hypothesized that protein intake from animal-sourced foods in recommended quantities could support normal weight and length gain and lower the risk of undernutrition associated with similar amounts of plant-based protein. However, higher protein intake, especially from milk protein, may be linked to increased body fat via plasma amino acids and the growth hormone-IGF axis.

**Conclusions:**

The results of this study will provide data on current complementary feeding practices, focusing on protein and iron intake in Thai infants. This information, combined with data on associations with infant growth and iron status, will help inform complementary feeding recommendations for this population and may be found relevant to other settings experiencing the double burden of malnutrition.

**International Registered Report Identifier (IRRID):**

DERR1-10.2196/18112

## Introduction

In 2016, while 52 and 155 million children around the globe were suffering from wasting and stunting, 41 million children under the age of 5 years were overweight or obese [1]. Therefore, the United Nations General Assembly launched a new policy, the United Nations Decade of Action on Nutrition from 2016 to 2025. The policy aims to end hunger and eradicate all forms of malnutrition worldwide [1]. In this proclamation, the double burden of malnutrition, the coexistence of undernutrition, overweight, obesity, and diet-related noncommunicable diseases are highlighted as an emerging public health problem in many countries experiencing socioeconomic transition. In order to achieve the goals of the proclamation, early life nutrition, especially during the first 1000 days of life, has been identified as one of the primary targets of intervention [2].

Along with optimal maternal nutrition and exclusive breastfeeding until 6 months of age, complementary feeding plays a pivotal role in early life nutrition from the age of 6 to 24 months. This period is also the most challenging, as a systematic review indicated that no single intervention can optimize growth outcomes for infants living in different circumstances with variations in the availability of micronutrient-rich foods, degree of household food insecurity, and traditional complementary feeding practices [3]. Among various topics related to complementary feeding, dietary protein is interesting as it is linked to all forms of malnutrition.

Protein is an essential macronutrient needed to build organ systems and body structures and mediates many physiological functions throughout life. For infants and young children, protein requirements per kg body weight are higher than any other age groups due to their rapid growth [4]. In addition, the proportion of energy from protein abruptly changes from 5% to around 15% of total energy intake when breastfed infants are introduced to complementary foods [5]. According to current evidence, insufficient protein intake during complementary feeding can contribute to undernutrition [6-8], whereas too much may increase the risk of overweight and obesity in later life [9-13].

Nevertheless, it is not only the amount of dietary protein that matters but also the source. Dietary protein comes from either animals or plants. Some studies have shown a link between protein sources and growth via plasma amino acids and the growth hormone—insulin-like growth factor I (IGF-1) axis. Semba et al demonstrated that stunted children had lower levels of plasma essential amino acids [14]. In contrast, a multicenter randomized controlled trial in 5 European countries showed that plasma Leucine and IGF-1 were positively associated with body mass index z-score (BMIZ) in infants who received high protein intake from infant formula [15]. These findings have two important implications. First, protein from animal-sourced foods such as milk, meat, and eggs provides all essential amino acids, while plant-based proteins (cereals, legumes, vegetables) usually lack one or two essential amino acids. Thus, it can be assumed that the effect of dietary protein on growth is more closely related to protein source than quantity. Second, as the proportion of leucine in the amino acid content of whey is higher in milk than that in meat (14% vs 8%, respectively) [16], protein intake from nondairy animal-sourced foods may not have the same influence on BMIZ as similar intake from milk. However, few studies have measured body composition as it relates to the intake of different protein sources.

Most evidence comes from two separate paradigms. The first has focused on lower- and middle-income countries where the researchers try to encourage higher protein intake in terms of both quantity and quality to overcome undernutrition, while the second paradigm is emerging in higher-income settings where researchers are aiming to prevent obesity by reducing the protein intake of infants and young children. As a result of these separate approaches, it is difficult to define guidelines for countries that are now facing the double burden of malnutrition, the majority of which are low- to middle-income countries.

Thailand is a country facing the double burden of malnutrition. The latest national and international surveys demonstrate a slowly declining percentage of childhood stunting, a high prevalence of iron deficiency, and rapidly increasing proportions of overweight, obesity, and diet-related noncommunicable diseases at a population level [17-19]. However, there have been no recent studies on protein intake among Thai infants. Although the latest Thai dietary reference intakes recommend a protein intake of 1.56 g/kg/day for Thai infants aged 6-11 months [20], there have been no clinical studies to support the adequacy of this recommendation in Thai infants as the recommendation is adapted from international guidelines [4].

### Aims and Hypotheses

We aim to understand the impact of dietary protein in early life using a holistic approach. This study will fill some of the knowledge gaps related to underlying mechanisms through the following objectives and hypotheses:

We will investigate the associations between the amounts and sources of dietary protein typically provided to Thai infants aged 6 to 12 months and changes in growth, including weight-for-age z-score (WAZ), weight-for-length z-score (WLZ), length-for-age z-score (LAZ), and BMIZ over 6-12 months. We will test the hypothesis that protein intake from animal-sourced foods in recommended quantities can support normal weight and length gain and reduce the risk of undernutrition associated with similar amounts of plant-based protein.We will investigate the associations between the amounts and sources of dietary protein typically provided to Thai infants aged 6 to 12 months and body composition at 12 months of age. We will test the hypothesis that a higher intake of protein from animal-sourced foods, especially dairy protein, is associated with an increased proportion of body fat during infancy.We will investigate the associations between complementary foods that provide different amounts of protein from animal-sourced foods and plant-based diets typically provided to Thai infants aged 6 to 12 months with iron status at 12 months of age. We will test the hypothesis that the timely introduction of protein from animal-sourced foods, especially red meat in the recommended amount, is associated with improved iron status and lower risk of iron deficiency anemia, without increasing the risk of overweight/obesity.We will investigate the possible mechanisms linking dietary protein and growth in early life through metabolomic processes. We will test the hypothesis that high protein intake from animal-sourced foods is associated with increased plasma essential amino acids, which may be correlated with concentrations of growth hormone, IGF-1, and IGFBP-3.

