### Statistical Analysis

There are two main parts of the statistical analysis. First, we will summarize the population characteristics of milk feeding, complementary feeding, and prevalence of undernutrition, overweight/obesity, and iron deficiency. Second, we will examine the associations between protein intake and source during complementary feeding and the outcomes specified in the objectives and hypotheses. All statistical tests will be considered significant when the *P* value is <.05 or 95% CIs of odds ratios do not include 1.

Descriptive data will be presented as mean (SD), median with interquartile range, or percentages depending on data type and distribution. These data will include demographic characteristics of infants and families, breastfeeding rate, age of the first introduction of complementary feeding, details of complementary feeding and energy/nutrient intake at each time point, average growth parameters at each time point, growth trajectory, and the prevalence of malnutrition (including wasting, stunting, overweight/ obesity, iron deficiency, iron deficiency anemia).

Protein intake at each time point, both total and separated by dietary source (ie, dairy protein, nondiary animal-based protein, and plant-based protein), will be considered as primary predictors to examine associations between protein intake and outcomes. To investigate associations between those predictors and continuous outcomes such as growth z-scores, percentage of body fat/fat-free mass, and blood parameters, we will use linear regression and correlation models (Pearson or Spearman correlation) for either univariate or multivariate analysis. For multivariate analysis, covariates will be selected for each of the dependent outcomes from previous research publications and our univariate analyses. Additionally, we intend to apply the directed acyclic graphs identifying covariates to reduce confounders [33]. If the dependent outcomes are categorical data such as nutritional status or iron status, binary or logistic regression analysis will be used as the main models.

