### Sample Size Calculation

We used the two-different means formulae [35] to calculate the sample size required to detect a 0.5 SD difference in growth parameters (WAZ, WLZ, and LAZ) between infants who receive red meat frequently and less frequently from 6-12 months of age (Textbox 2).

Sample size calculation.Mean difference 0.5 SDSD 1.0 (adopted from Olaya G et al [36])Power 80%, significance level .05Sample size: 126 participantsWith surplus 15% drop out rate, the final number is 148 participants

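### Hypothesis 2 singles out dairy protein for body fat, but the stated analysis does not test dairy against other animal protein

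*Protocol article*

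**What the plan says.** Under Aims and Hypotheses, the second hypothesis is that "a higher intake of protein from animal-sourced foods, especially dairy protein, is associated with an increased proportion of body fat during infancy". The outcome is body composition at 12 months, which is a secondary outcome. The Introduction gives the rationale at matched amounts: "protein intake from nondairy animal-sourced foods may not have the same influence on BMIZ as similar intake from milk".

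The Statistical Analysis section then states that protein intake, "both total and separated by dietary source (ie, dairy protein, nondiary animal-based protein, and plant-based protein), will be considered as primary predictors". For continuous outcomes, including percentage body fat, "we will use linear regression and correlation models (Pearson or Spearman correlation) for either univariate or multivariate analysis". The criterion for every test is that the P "value is <.05 or 95% CIs of odds ratios do not include 1". The section also plans covariate selection with directed acyclic graphs and a comparison of low with high protein intake groups. It names no comparison of the dairy and nondairy animal coefficients.

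**The concern.** The hypothesis has two parts: that animal-sourced protein is associated with more body fat, and that this is more so for dairy. The stated analysis addresses the first part. The second needs an estimate of the difference between two slopes, and none is named.

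Without it, the natural evidence for dairy would be that its P value crosses .05 while that for nondairy animal protein does not, or that its correlation is larger. Neither shows a difference in effect per gram. A P value depends on the spread of the intake and on chance as well as on the slope. A correlation rises with the spread even when the slope is fixed.

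The Abstract says that the results will help inform complementary feeding recommendations, and the Discussion says that they may be used to plan an intervention study. A ranking of dairy above meat, egg or fish protein that was never tested could enter both.

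**Working it through.** **The plan's own figure.** The sample size was set "to detect a 0.5 SD difference in growth parameters (WAZ, WLZ, and LAZ) between infants who receive red meat frequently and less frequently". With difference 0.5, SD 1.0, two-sided .05 and 80% power, n per group = 2 × (1.96 + 0.84)² × 1.0² / 0.5² = 62.7, rounded up to 63, so 126 in total. Allowing 15% dropout, 126 / 0.85 = 148.2, against 148 stated. The figure reproduces. It concerns red meat and growth z-scores, so it says nothing about power for dairy against nondairy protein and body fat.

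**Inputs for the check.** From the article: N = 146 ("A total of 150 participants were enrolled, and 146 completed the study"), the three sources, linear regression and the .05 level. Assumed, because the article gives no figures: two-sided tests, normally distributed intakes, residual SD 1, nondairy intake SD 1, identical per-gram slopes of 0.10, 0.15 or 0.20 residual SD per nondairy SD, and the ratio of dairy to nondairy intake SD. All three sources were fitted in one model, with 6,000 simulated cohorts per setting.

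**Equal spread.** With uncorrelated intakes, P(dairy significant, nondairy not) ≈ p_d × (1 − p_n), where p_d and p_n are the powers for the two slopes.
- Slope 0.10: 0.222 × (1 − 0.214) = 0.17; simulated 17%, reverse pattern 16%.
- Slope 0.15: 0.441 × (1 − 0.423) = 0.25; simulated 25%, reverse 23%.
- Slope 0.20: 0.657 × (1 − 0.654) = 0.23; simulated 22%, reverse 22%.
- At 80% power for both: 0.8 × 0.2 = 0.16.

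With equal powers p(1 − p) cannot exceed 25%, hence about 16% to 25% over these settings. In the three simulated settings one source alone is significant in 33%, 48% and 44% of studies, although the slopes are the same.

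**Unequal spread.** Percentage of studies with dairy only significant (nondairy only in brackets), uncorrelated intakes:

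| Dairy SD / nondairy SD | Slope 0.10 | Slope 0.15 | Slope 0.20 |
|---|---|---|---|
| 0.5 | 7 (19) | 8 (37) | 7 (51) |
| 1 | 17 (16) | 25 (23) | 22 (22) |
| 1.5 | 32 (12) | 44 (10) | 33 (4) |
| 2 | 51 (8) | 54 (2) | 33 (0.3) |
| 3 | 74 (1) | 57 (0) | 34 (0) |

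With a true slope of zero, each pattern appears in about 5%. With an intake correlation of −0.3 the pattern is similar: 14% to 19% dairy only at ratio 1, and 46%, 55% and 37% at ratio 2.

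**Correlations.** With uncorrelated intakes, r = slope × intake SD / outcome SD. For slope 0.15 and SD ratio 2, the outcome SD is √(1 + 0.15² × (4 + 1)) = 1.055. Then r = 0.30 / 1.055 = 0.28 for dairy and 0.15 / 1.055 = 0.14 for nondairy: twice as large, at the same effect per gram.

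**Direct contrast.** The test of dairy slope minus nondairy slope rejected in 4.4% to 5.6% of runs in every setting. That counts both directions, so by symmetry about half would favour dairy.

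**Price in precision.** With equal, uncorrelated spread, the SE of each slope is about 1/√146 = 0.083, and that of the difference √2 × 0.083 = 0.117. At 80% power the detectable sizes are about 2.80 × 0.083 = 0.23 for a slope and 2.80 × 0.117 = 0.33 for the difference.

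**The case against.** The strongest reply is that this is a short methods section in a journal article. Which sources share a model and which coefficients are contrasted is often left to a fuller plan, which is not at hand and may contain the contrast. Nothing in the section rules it out. Multivariate analysis permits a joint model, and regression slopes per unit of intake do not scale with spread as correlations do. This stands in part: no one can say that the contrast will be omitted. But the article does fix the hypothesis, predictors, methods and criterion, and as fixed the criterion does not answer the comparative part of the hypothesis.

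A reader might infer that dairy will look special because its intake varies more, for example because breastfed and formula-fed infants are mixed. The documents do not support that. No intake SD is given for any source. Textbox 1 excludes infant and follow-on formula from complementary feeding, which leaves it unclear whether formula protein counts as dairy, and Study Setting says that one clinic prohibits formula. If dairy varies less, nondairy protein is favoured instead.

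A reader might also infer that the authors intend to rank sources by P value. No section says so.

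Finally, the Introduction says only that the influences may differ, and BMIZ belongs to the first objective. The mismatch therefore concerns body fat, a secondary outcome.

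**Conclusion.** The point holds as a mismatch between a comparative hypothesis and an analysis that states no comparison. It does not depend on which source varies more. With equal slopes and equal, uncorrelated spread, a dairy-only result appears in about 16% to 25% of studies and the mirror image about as often, against about 5% for the direct contrast. Unequal spread raises the frequency and sets the direction: at SD ratios of 1.5 to 3 the simulated dairy-only frequency is 32% to 74%.

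These percentages rest on assumed slopes, spreads and normal intakes. They are not a forecast for this cohort: the dairy-only pattern falls to about 5% if there is no effect, and becomes less common once slopes are large enough for both sources to be significant. What is certain is narrower: separate tests or correlations cannot support singling out dairy, and a slope difference with its interval can.

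**What to change.** For percentage body fat at 12 months, state that one covariate-adjusted linear model will contain dairy, nondairy animal and plant protein together on a common scale, g/day or g/kg/day. Handle energy intake and body size through the directed acyclic graph already planned. State whether infant and follow-on formula protein counts as dairy.

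Report the dairy minus nondairy animal slope with its 95% CI. Single out dairy only if that interval lies wholly above zero; otherwise report the two slopes as not distinguished. The same contrast may be reported for BMIZ under the first objective.

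This takes a sentence or two in the plan and one linear contrast per outcome, with no new data. The Results section describes laboratory analyses as still under way, so the contrast could be specified before the body-fat results are seen. The downside is precision: the contrast is less precise than either slope in the settings examined, so the claim about dairy becomes harder to make.

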## Methods

### Study Design and Approval

#### Study Design

This protocol is for a multicenter, prospective cohort study.

#### Study Setting

This cohort study will be performed in three well-baby clinics in Chiang Mai, Thailand. We selected these well-baby clinics based on their locations and opening times that did not overlap, allowing the single investigator to attend all clinic sessions. Two study sites are in urban areas, and another is in a suburban area. One clinic in the urban area is in a maternal and child-friendly hospital where infant formula is prohibited, and the breastfeeding rate is higher than the average for other Thai hospitals.

#### Ethics Approval

The study will be conducted in accordance with the Declaration of Helsinki. Participation is voluntary, and subjects can withdraw from the study at any stage. The study enrolment is completed when written informed consent is obtained from the legal guardian. Identifiable data of participants and their families will be kept in a secure location, only accessible to the researchers. Ethics approvals have been obtained from the University College London Ethics committee, United Kingdom (Approval ID: 12551/001), and the Ethics Committee of the Faculty of Medicine, Chiang Mai University, Thailand (Approval ID: PED-2561-05287).

### Definitions

Key terms are defined in Textbox 1.

Definitions.*Complementary feeding* is all solid and liquid foods other than breast milk or infant and follow-on formula, as suggested by the European Food Safety Authority (EFSA) [21] and the position papers from the European Society for Pediatric Gastroenterology Hepatology and Nutrition [22].*Stunting* is defined as LAZ <2 SD below the median of the WHO growth standards for children aged under 5 years [23].*Wasting* is defined as WLZ <2 SD below the median of the WHO child growth standards for children aged under 5 years [23].*Underweight* is defined as WAZ is <2 SD below the median of the WHO child growth standards for children aged under 5 years [23].*Overweight* is defined as WLZ >2 SD above the median of the WHO child growth standards for children aged under 5 years [24].*Obesity* is defined as WLZ >3 SD above the median of the WHO child growth standards for children aged under 5 years [24].*Iron deficiency* is defined by at least one of the following serum ferritin less than 12 μg/L (if erythrocyte sedimentation rate, ESR ≤10 mm/h) or serum ferritin less than 30 μg/L (if ESR >10 mm/h) or serum transferrin saturation less than 16% [25].*Iron deficiency anemia* is defined as iron deficiency plus hemoglobin <11.0 g/dL [25].*Exclusive breastfeeding* means the infant receives only breast milk without anything else except for water and necessary medication.*Predominant breastfeeding* means that breast milk is more than 50% of daily milk intake after 6 months of age.*Predominant formula feeding* means that infant or follow-on formula provides more than 50% of daily milk intake and for a longer period than breastfeeding.*Animal-sourced food* is defined as any food that is edible and originates from animals such as milk, dairy products, meat (ie, beef, pork, poultry), processed meats, fishes, insects, and eggs.*Plant-based protein* is defined as dietary proteins that are edible and originate from plants such as cereals, lentils, legumes, nuts, and vegetables.The *primary caregiver* is defined as the person who spends the most time looking after the infant on a daily basis.

